## 9.4. Treatments

### 9.4.1 Treatment Administered

Collection of convalescent plasma

Donor eligibility

Convalescent plasma donors will be recruited in a population of patients that were infected with SARS-CoV-2 and recovered. Potential donors must at least fulfill national legal requirements for eligibility of donors to donate blood or plasma. The collection of blood products is defined by the Belgian Blood legislation (Law July 5th 1994, and R.D. April 4th 1996).

Potential donors can be identified through collaboration with treating hospitals or practitioners or via direct search for patients cured from COVID-19.

Personal data sharing strategies must comply with national and EU data protection rules.

The following criteria for donor eligibility will be applied additional to national legal requirements:

1. a asymptomatic donor with prior diagnosis of COVID-19 documented by a laboratory test or a clinical picture with radiological confirmation of COVID-19.
2. at least 28 days will have passed since full recovery and disappearance of the symptoms. Blood establishments might modify the timing of plasma collection when findings regarding the timing of optimal and maximal antibody production in those who have recovered from COVID-19 become available and is confirmed acceptable by AFMPS/FAGG.
3. Donors without a history of blood transfusion or without history of tissue or organ transplantation.
4. Donors without positive screening for irregular antibodies.
5. Female donors can only be recruited if either no history of pregnancy or if tested and found negative for anti-HLA/HPA/HNA antibodies using a validated assay. Standard donor criteria for blood or plasma donation must be met.
6. Informed consent in accordance with the Belgian Blood Legislation and national and EU data protection rules.

Plasma collection:

Collection, processing and storage

Donors will ideally donate plasma by plasmapheresis, but where apheresis is not sufficient to supply enough plasma, whole blood can also be collected, with plasma separation in the blood establishment. Eligible plasmapheresis donors are allowed, according to Belgian Blood legislation, to donate a total volume of 650 ml per session, 2 liters per month and 15 liters per year. The inter-donation interval is at least one week. Plasma obtained by plasmapheresis and processed will be split before freezing into 2-

3 separate units (e.g. 3x200 ml). Final products will be specifically labelled as COVID-19 Convalescent Plasma and stored in a dedicated location. The processing that is routinely used for pathogen reduction by Methylene Blue will be applied according to standard practice in the blood establishment.

The production process and product characteristics will comply with current Belgian Blood legislation. For this trial, volumes will be between 200 and 250 ml. The product can be stored for 36 months at a temperature below -25°C or for 3 months at a temperature between -18°C and -25°C.

Data collected from donors

The following data will be collected:

- Date of nasopharyngeal swab that subsequently proved SARS-CoV-2-positive by PCR (or alternative date of radiological confirmation)
- Time from diagnosis until resolution of symptoms

Testing of donated plasma

Defined SARS-CoV-2 neutralizing antibody titers will be measured in the donated plasma. A Blood or Plasma sample from all donors will be stored in tube with gel for that purpose and for testing of antibody specificities.

Blood establishments will determine SARS-CoV-2 neutralizing antibody titers at or prior to the first donation to allow the selection of donors with high titers. The neutralizing antibody titers will be repeated with a maximal interval of one month. Samples of donations done in-between will be stored for later testing.

The Blood Establishment will qualify donations from donors with neutralizing antibody titers greater or equal to 1/320 as appropriate for this study. In case of shortage of plasma with a titer greater or equal to 1/320 on the moment of patient enrolment, plasma from convalescent donors with a titer of at least 1/80 will be released for transfusion.

If an adequate correlation between neutralizing activity and Elisa antibody testing for SARS-CoV2 were to be demonstrated by a validation report to be approved by the sponsor, this assay could replace the test for neutralizing antibodies. Additional archive samples of the donated plasma will be saved for reference studies e.g. frozen aliquots from plasma samples taken at the time of donation.

When the measured neutralizing activity in the collected plasma is considered too low, the plasma will be made available for other use.

Convalescent Plasma and Dosing Regimen

Patients in the intervention arm will get 2 units (400-500 mL in total) of convalescent plasma. A single unit has a volume that ranges from 200mL to 250mL. Determination of ABO compatibility will follow local procedures and plasma will be transfused within six hour after thawing. Plasma will be provided by the

local blood bank. Convalescent plasma will be stored in a limited number of places. Products can only be shipped to the local site only when the patient is randomized.

#### **9.4.2 Identity of Investigational Product (s)**

Intervention arm: 2 units (400-500 mL in total) of convalescent plasma. The treatment will be administered within 24 hours of inclusion in the study, through a venous line over at least 2 hours. (to prevent potential adverse effect of fluid overload).

Control arm: no plasma

#### **9.4.3 Selection of Doses in the Study**

Interventional group: 2 units (400-500 mL in total) of convalescent plasma with at least 1/320 PRNT50 of neutralizing antibodies. Each unit will preferably come from two different donors. Control group: no plasma.

#### **9.4.4 No blinding**

We chose not to blind the treatments because the principal endpoint (day 28 mortality) is an objective one.

#### **9.4.5 Prior and concomitant therapy**

At the present time, no specific treatment has been proven to improve the outcome of COVID-19 critically ill patients beside the conventional support of organ failure. The treatments administered in compassionate use on a frequent basis (*i.e.* hydroxychloroquine or azithromycin) or on selected cases (*i.e.* anti-HIV or Ebola antivirals, anti-cytokines or anti-cytokine receptors ...) are likely to be dispatched similarly in the randomization arms and can be used in the patients included in this trial. Their use will be assessed and provided in the descriptive results of the population.

No particular drug-drug interactions are anticipated.

#### **9.4.6 Treatment Compliance**

The patients included will be totally dependent from the organ supply they will receive for life support in the intensive care unit. The treatment will be administered in a single administration. The issue of compliance is therefore not applicable.

### **9.5. Study Procedures**

#### **9.5.1 Availability of the study product**

Prior to request informed consent from the patient, his/her representative or a impartial witness (see below), the investigator will contact the CCC St-Luc. The CCC St Luc will check the eligibility of the patient with the local investigator or his/her representative for the study. The CCC St Luc will check the

[figure not shown]

website of the Red-Cross to ascertain that the convalescent plasma of the patient's ABO group at a titer of 1/320 is available for delivery to the site. In case of shortage of plasma with a titer greater or equal to 1/320 on the moment of patient enrolment, plasma from convalescent donors with a titer of at least 1/80 will be released for transfusion. If the patient is eligible and the plasma is available, the informed consent will be obtained according to the procedure indicated in the "participant consent" paragraph.

### **9.5.2 Participant consent**

The eligible patients will be unable to speak – due to tracheal intubation - and most often likely not able to understand the information about the benefits and risks of the trial – due to sedation and/or confusion due to COVID-induced sepsis. Their relatives will likely be only contacted by phone according to the guidelines of the participating ICU, which most frequently preclude access of visitors to the hospitals due to the pandemic aspect of COVID-19.

The capability to be informed and to provide their consent will be assessed for all potential patients. If the written consent of the patient cannot be obtained, it will be asked from a relative / legal representative of the patient over the phone (preferably through video conference) and the form will be sent for signature to the relative and returned by the him/her by email. In the absence of written consent due to incapacity of the patient or to impossibility to have a contact with the relative / legal representative, the investigator will have to obtain the written approval from an impartial witness. The witness can be a physician from another department of the hospital.

In case of inclusion without the written consent of the patient and in case of recovery, his/her consent to continue to participate and/or to use his/her personal data will be requested.

### **9.5.3 Process of randomization**

The process of randomization will be performed through a standard randomization system (UCL clinical trial center, Pr [name]) either directly through the eCRF system or by the CCC St Luc. The randomization process will be stratified according to the delay from tracheal intubation to inclusion (" $\leq$  48 hours"; "between 48 hours and 5 days"). A response to telephone calls for any issue regarding the inclusion criteria will be available 24/7 (see "availability of the study product" paragraph).

The treatment (intervention versus control) will be allocated in 2 arms in a 1:1 ratio. The randomization table will be made of permuted block size provided by the statistician.

### **9.5.4 Visits**

#### **9.5.4.1 Screening**

The principal investigator of each participating center will organize the detection of potentially eligible patients, based on medical history and inclusion criteria available in the patient's record, gather consent to participate according to the study protocol. The response must be yes to all the following questions:

[figure not shown]

- Age > 18 years
- Hospitalisation in a ICU participating to the study
- extended interstitial pneumonia on CT scan or chest X-ray, consistent with viral pneumonia, within 10 days prior to inclusion
- Positive result of SARS-CoV-2 PCR test, or any emerging and validated diagnostic laboratory test for COVID-19, within 15 days prior to inclusion
- Under mechanical ventilation administered through an endotracheal tube, for no more than 5 days
- prior Clinical Frailty Scale < 6
- written consent of the patient, or – if impossible - of a relative acting as the legal representative, or – if impossible - of a physician from a non-participating department of the same hospital acting as an impartial witness (see trial procedures)
- No pregnancy
- No prior episode of transfusion-related side effect
- No medical decision to limit therapy
- No current participation in another trial testing a COVID-19 therapy

#### **9.5.4.2 Inclusion visit (Day 1)**

Parameters will be obtained as part of the routine clinical care. They will include

- Date of Birth
- Male/Female
- Weight kg
- Height cm
- Clinical frailty scale (appendix F)
- ADL (estimated before COVID-19)
- EQ-5D-5L (estimated before COVID-19)
- marital status
- highest diploma
- work situation
- Reference serum creatinine

Comorbidities (yes/no)

- Hypertension
- Coronary heart disease
- Congestive heart failures

- Chronic obstructive pulmonary diseases
- Asthma
- Fibrotic pulmonary disease
- Neurological disease
- Connective tissue disease
- Diabetes
- Chronic renal failure
- Cirrhosis
- Active solid cancer without metastases
- Active solid cancer with metastases
- Haematological cancer
- AIDS/HIV

#### Recent medications within the last 3 months

- Steroids
- Immunotherapy
- Anti-cancer chemotherapy
- Immunosuppressive drugs

#### Current hospitalisation

- Date of hospital admission
- Date of Covid infection diagnosis
- Date of ICU admission
- Date of Intubation
- Date of study inclusion

#### Clinical findings

- APACHE II score calculation, based on the following criteria
- SOFA score calculation, based on the following criteria
- Glasgow coma score
- Systolic arterial pressure
- Mean arterial pressure
- Need of vasopressor
- Need of ECMO
- PEEP
- Pplat
- Prone positioning

- 24 h diuresis
- Need of renal replacement therapy
- Highest temperature

#### Biologic findings

- Haemoglobin
- Haematocrit
- Platelet count
- White blood cells count
- Neutrophil
- Lymphocyte
- PaO2
- FiO2
- Na
- K
- urea
- creatinin
- protein
- bilirubin
- ferritin
- CRP
- Ddimer
- fibrinogen
- LDH
- TGO
- TGP
- CPK
- Time of administration of the convalescent plasma (in days from disease onset)
- Number, volume and anti-body titre of transfused units
- Any serious adverse reactions or events possibly linked to the transfusion
- WHO progression scale
- Total and neutralizing antibodies to SARS-CoV-2 (centralized)

#### **9.5.4.3 Assessments visits D7 (+-1 day)**

- SOFA score calculation
- Glasgow coma score

- Peep level
- Plateau pressure
- tidal Volume
- Respiratory rate
- FiO2
- PaO2
- PaCO2
- Mean arterial pressure
- Inotropic or vasopressor support for at least one hour
  - Dopamine,
  - dobutamine,
  - noradrenaline < 0,1 µg/kg/min
  - noradrenaline > 0,1 µg/kg/min,
  - adrenaline <0,1 µg/kg/min,
  - adrenaline > 0,1 µg/kg/min,
  - vasopressin/-analogues
- Creatinine
- 24 h diuresis
- Platelet count
- Bilirubin
- CRP
- WBC count
- Ferritin
- Lymphocyte count
- Tracheal aspirate for SARS-CoV-2 viral load, expressed as cycle threshold, assessment
- WHO progression scale
- Total and neutralizing antibodies to SARS-CoV-2 (centralized)

#### **9.5.4.4 Assesment visit D14 (+-1 day)**

- SOFA score calculation
- Glasgow coma score
- Peep level
- Plateau pressure
- tidal Volume
- Respiratory rate

- FiO2
- PaO2
- PaCO2
- Mean arterial pressure
- Inotropic or vasopressor support for at least one hour
  - Dopamin,
  - dobutamin,
  - noradrenalin < 0,1 µg/kg/min
  - noradrenalin > 0,1 µg/kg/min,
  - adrenalin < 0,1 µg/kg/min,
  - adrenalin > 0,1 µg/kg/min,
  - vasopressin/-analogues
  
- Creatinine
- 24 h diuresis
- Platelet count
- Bilirubin
- CRP
- WBC count
- Ferritin
- Lymphocyte count
- Tracheal aspirate for SARS-CoV-2 viral load, expressed as cycle threshold, assessment

#### **9.5.4.5 Assesment visit D21 (+-1 day)**

- SOFA score calculation
- Glasgow coma score
- Peep level
- Plateau pressure
- tidal Volume
- Respiratory rate
- FiO2
- PaO2
- PaCO2
- Mean arterial pressure
- Inotropic or vasopressor support for at least one hour

- Dopamin,
  - dobutamin,
  - noradrenalin < 0,1 µg/kg/min
  - noradrenalin > 0,1 µg/kg/min,
  - adrenalin < 0,1 µg/kg/min,
  - adrenalin > 0,1 µg/kg/min,
  - vasopressin/-analogues
- 
- Creatinine
  - 24 h diuresis
  - Platelet count
  - Bilirubin
  - CRP
  - WBC count
  - Ferritin
  - Lymphocyte count
  - Tracheal aspirate for SARS-CoV-2 viral load, expressed as cycle threshold, assessment

#### **9.5.4.6 Assessment visit D28 (+-1 day)**

- SOFA score calculation
- Glasgow coma score
- Peep level
- Plateau pressure
- tidal Volume
- Respiratory rate
- FiO2
- PaO2
- PaCO2
- Mean arterial pressure
- Inotropic or vasopressor support for at least one hour
  - Dopamin,
  - dobutamin,
  - noradrenalin < 0,1 µg/kg/min
  - noradrenalin > 0,1 µg/kg/min,
  - adrenalin < 0,1 µg/kg/min,
  - adrenalin > 0,1 µg/kg/min,

- vasopressin/-analogues
- Creatinin
- 24 h diuresis
- Platelet count
- Bilirubin
- CRP
- WBC count
- Ferritin
- Lymphocyte count
- Tracheal aspirate for SARS-CoV-2 viral load, expressed as cycle threshold, assessment
- Total and neutralizing antibodies to SARS-CoV-2 (centralized)

#### **9.5.4.7 ICU discharge**

- Date of ICU discharge
- WHO progression scale

#### **9.5.4.8 Assessment visit Day 90 (+-15 days)**

- Vital status (dead/alive)
- Body weight
- Return to work (Y/N)
- ADL scale (appendix C)
- Anxiety depression scale (appendix D)
- EQ-5D-5L scale (appendix E)
- Total and neutralizing antibodies to SARS-CoV-2 (centralized)

#### **9.5.4.9 Assessment visit Day 365 (+- 30 days)**

- Vital status (dead/alive)
- Body weight
- Return to work (Y/N)
- ADL scale

- Anxiety depression scale
- EQ-5D-5L scale

This visit will be performed by phone call or by courier.

#### **9.5.4.10 Discharge from the hospital**

- Date of ICU discharge
- Patient alive (Y/N)
  - If Yes :
    - Date of last extubation
    - Destination (Home, revalidation, acute care unit)
- 
- Tracheostomy during the ICU stay
  - Y/N
  - date
- Date of hospital discharge

### **9.5.5 Data to be shared at the European level regarding convalescent plasma use**

[https://ec.europa.eu/health/blood\\_tissues\\_organs/covid-19\\_en](https://ec.europa.eu/health/blood_tissues_organs/covid-19_en)

Register:

[https://ec.europa.eu/health/sites/health/files/blood\\_tissues\\_organs/docs/guidance\\_plasma\\_covid19\\_en.pdf](https://ec.europa.eu/health/sites/health/files/blood_tissues_organs/docs/guidance_plasma_covid19_en.pdf)

- Gender, age range (30-39, 40-49 etc.), co-morbidities
- Transfusion time point (in days from disease onset)
- Number, volume and anti-body titre of transfused unit(s)
- Therapies administered to the patient in parallel (other than supportive care)
- Clinical symptoms and laboratory parameters– according to the disease progression scale (Appendix B) at the following time points:
  - Prior to transfusion

- 5 days after transfusion
- At discharge (if the patient survives)
- Any serious adverse reactions or events possibly linked to the transfusion
- Length of hospitalisation (if no death).

#### **9.5.12 Assessment visits in case of discharge before day 90**

In case of acute care hospital discharge before day 90, the day 90 visit will be performed by phone call.

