### 7.2. Secondary

The secondary objectives are to assess:

- the efficacy of convalescent plasma
  - o to reduce day-90 mortality
  - o to reduce the duration of mechanical ventilation over the 28 days after inclusion,
  - o to reduce the severity of organ failure over the 28 days after inclusion,
  - o to reduce the use of organ support over the 28 days after inclusion
  - o to reduce the viral load, expressed as cycle threshold, over the 28 days after inclusion
  - o to reduce the intensity of the inflammatory response during the 28 days following inclusion.
  - o to reduce the acute care hospital length of stay
  - o to increase the functional, psychological state and quality of life at day 90 and at day 365 after inclusion
  - o to assess the impact of convalescent plasma on sero-conversion against SARS-CoV-2
- the incidence of adverse events related to plasma transfusion
- the incidence of adverse events related to organ support.

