### 7.3. Endpoints

The principal endpoint will be vital status (dead/alive) at day 28

The secondary endpoints will be

- day-90 mortality
- number of ventilator-free days at day 28
- number of renal replacement therapy-free days at day 28
- number of vasopressors-free days at day 28
- use of ECMO before day 28
- value of the SOFA score at days 7, 14 and 28 [1] (see appendix A).
- changes in SOFA scores over the following 7, 14 and 28 days
- value of the SARS-CoV-2 viral load, expressed as cycle threshold, [2] in the tracheal aspirates (for intubated patients) or nasopharyngeal swabs (for extubated patients) at days 7, 14 and 28
- blood C reactive protein (CRP) concentrations at days 7, 14 and 28
- length of stay in the acute care hospital
- location of the patients at day 90: acute care hospital, post-acute care hospital, long-term residency, home
- WHO progression scale prior transfusion, at day 7 and at discharge (see appendix B)
- Hospital Activity of Daily Living (ADL) functional score at day 90 and at day 365. [3] (see appendix C).
- Anxiety-depression evaluation scale at day 90 and at day 365. [4] (see appendix D ).
- Quality of life scale (EQ-5D-5L) at day 90 and at day 365. [5] (see appendix E).
- Transfusion-related adverse events within 7 days
- Sero-positivity to SARS-CoV-2 at days 1, 7, 28 and 90
- Adverse events related to standard of care (mechanical ventilation, prolonged decubitus, prone positioning...) such as:
  - o Ventilator associated pneumonia
  - o Secondary bacteremia [6]
  - o Deep vein thrombosis and pulmonary embolism
  - o Pressure ulcers, stage 2 to 4 (*i.e.* loss of skin, of tissue or of bone) [7]
  - o Ventilator induced baro-traumatism (pneumothorax, pneumo-mediastinum, sub-cutaneous emphysema) [8]
  - o Accidental ablation of tracheal or vascular device [9]
  - o Ventilator induced baro-traumatism (pneumothorax, pneumo-mediastinum, sub-cutaneous emphysema) [8]
  - o Accidental ablation of tracheal or vascular device [9]

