| Viral load (NP or tracheal PCR)      |           | x         | x               | x    | x    | x    |               |     |      |
| Clinical frailty scale               |           | x         |                 |      |      |      |               |     |      |
| Concomitant drugs against SARS-CoV-2 | x         | x         | x               | x    | x    | x    |               |     |      |
| Biological findings                  |           | x *a      | x *b            | x *b | x *b | x *b |               |     |      |
| 24h-diuresis                         |           | x         | x               | x    | x    | x    |               |     |      |
| Serum sample for central analysis    |           | x         | x               |      |      | x    |               | x   |      |
| Mechanical ventilation               |           | x         | x               | x    | x    | x    |               |     |      |
| Renal replacement therapy            |           | x         | x               | x    | x    | x    |               |     |      |

|                                           |  |   |   |   |   |   |  |   |   |
|-------------------------------------------|--|---|---|---|---|---|--|---|---|
| Vasoactive drugs                          |  | x | x | x | x | x |  |   |   |
| ECMO                                      |  | x | x | x | x | x |  |   |   |
| Nosocomial infections                     |  | x | x | x | x | x |  |   |   |
| Iatrogenic events                         |  | x | x | x | x | x |  |   |   |
| Adverse events &
Serious adverse event |  | x | x | x | x | x |  |   |   |
| ADL scale                                 |  | x |   |   |   |   |  | x | x |
| Anxiety-depression scale                  |  |   |   |   |   |   |  | x | x |
| EQ-5D-5L scale                            |  | x |   |   |   |   |  | x | x |

\* Please see section 9.5 for more details

a. Haemoglobin, Haematocrit, Platelet count, White blood cells count, Neutrophil, Lymphocyte, PaO2, FiO2, Na, K, urea, creatinin, protein, bilirubin, ferritin, CRP, Ddimer, fibrinogen, LDH, TGO, TGP, CPK

b. creatinin, platelet count, bilirubin, CRP, WBC count, Ferritin, Lymphocyt count

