## **9.6. Efficacy and Safety Variables**

### **9.6.1 Efficacy and Safety Measurements Assessed and Flow chart**

Measurements will be performed by the investigators and clinical research assistants during their stay in the hospital and during medical visits at each time of endpoints (days 7, 14, 28, 90) in case of hospital discharge, and by phone for day 365 endpoint.

Vital status, dependence on the ventilator and clinical and biological data to calculate the SOFA score will be collected from the patient's record. Viral load, expressed as cycle threshold, will be assessed from tracheal aspirates or naso-pharyngeal swabs and RT-PCR assessment by the usual technique of the routine laboratory. Adverse events possibly related to study intervention will be collected prospectively, according to definitions of iatrogenic events, transfusion-related events and nosocomial infections by the investigator and the clinical research assistant in charge of the study. Scales assessing functional state, psychological state and quality of life will be collected at day 90 visit and over the phone at day 365 visit by a clinical research assistant dedicated to this task by the coordinating center. The adverse events will be collected and severity rating according to Belgian guidelines.

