Regarding the secondary endpoints, quantitative values between groups will be compared by Student t-test or non-parametric Wilcoxon for the SOFA score (at different time points), viral load of SARS-CoV-2 (at different time points), circulating CRP (at different time points), ADL score at day 90, anxiety-depression scale at day 90, sero-conversion. Poisson regression analysis will be considered to analyse number of ventilator-free days up to day 28. Comparison of proportions will be applied to compare location of patient at day 90, as well as presence of various adverse events. If descriptive analysis revealed the presence of potential confounding factors, appropriate multivariate analysis will then be considered.

The two-sided level of significance used in this trial is 5%. Statistical analyses will be carried out using SAS (version 9.4 for Windows) statistical package.

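### Section 9.5.12 makes the day-90 visit a phone call after discharge, which conflicts with the day-90 serum sample and puts at risk the time point least affected by transfused antibody

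*Protocol*

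**What the plan says.** Section 7.2 of the protocol sets a secondary objective "to assess the impact of convalescent plasma on sero-conversion against SARS-CoV-2". The matching endpoint in section 7.3, repeated in the synopsis, is "Sero-positivity to SARS-CoV-2 at days 1, 7, 28 and 90".

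The day-90 visit is described in four places:

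- Section 9.5.4.8 lists "Total and neutralizing antibodies to SARS-CoV-2 (centralized") among its assessments.
- The flow chart after section 9.5.14 has a row "Serum sample for central analysis", marked at D1, D7, D28 and D90.
- Section 9.5.12 says "In case of acute care hospital discharge before day 90, the day 90 visit will be performed by phone call".
- Section 9.6.1 says measurements are made "during medical visits at each time of endpoints (days 7, 14, 28, 90) in case of hospital discharge, and by phone for day 365 endpoint".

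The synopsis names antibody against the virus as the product's active ingredient. Section 9.4.2 gives it to the intervention arm within 24 hours of inclusion, and the control arm receives no plasma. The protocol gives no positivity threshold, does not separate transfused from endogenous antibody, and does not say whether the day-1 sample comes before the transfusion.

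Section 9.9 names "anxiety-depression scale at day 90, sero-conversion" in its list of quantitative variables for the t-test or Wilcoxon test. The same section assigns proportions to the chi-square test.

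**The concern.** Blood cannot be drawn over the phone. If 9.5.12 governs, every patient discharged from acute care before day 90 lacks the sample that 9.5.4.8, the flow chart and the endpoint list all require. The remaining patients are not a random subset: they are the ones who have recovered most slowly.

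Day 90 is also the sample that best serves the stated objective. Only one arm receives antibody as the treatment, so a positive result soon after transfusion in that arm may be the product, the patient's own response, or both. By day 90 the transfused part should have largely gone. Losing that sample leaves the objective resting on days 7 and 28, where the two sources are mixed. This has to be settled before patients reach day 90, because a sample not drawn cannot be recovered by a later analysis plan.

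**Working it through.** The protocol states no rate, threshold or power for this endpoint, so there is no figure to reproduce. The check is a comparison of text with three supporting calculations.

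**1. Compatibility of the day-90 passages**

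| Place | Day 90 after discharge | Serum obtainable? |
|---|---|---|
| 9.5.12 | phone call | no |
| 9.5.4.8 | visit with antibody assay | yes |
| Flow chart | central serum sample marked | yes |
| 9.6.1 | medical visit; phone only at day 365 | yes |

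Three places imply a blood draw and one rules it out for discharged patients. Patients still in acute care at day 90 are unaffected.

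**2. Samples at stake**

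Inputs from section 9.9: 250 per arm, control mortality 40%, absolute reduction 13.5 points, hence 40 − 13.5 = 26.5% in the plasma arm.

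Day-28 survivors = 250 × 0.60 + 250 × 0.735 = 150 + 183.75 ≈ 334. The synopsis figure of a 30% relative reduction gives 250 × 0.60 + 250 × 0.72 = 330, which changes nothing material.

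The discharged share is not in the documents. Over an assumed range, under 9.5.12:

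| Share discharged before day 90 (assumed) | Samples lost | Samples left |
|---|---|---|
| 50% | 167 | 167 |
| 70% | 234 | 100 |
| 90% | 300 | 33 |

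Under 9.6.1 the design loses none. The base is day-28 survivors, so deaths between days 28 and 90 would lower all these counts.

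**3. How much transfused antibody could remain**

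Inputs from the protocol: 400-500 mL, donor titre at least 1/320, or at least 1/80 in shortage. Assumptions: recipient plasma volume 2.5-3.5 L, IgG half-life 21 days, transfusion on day 1, recipient initially negative. The lower ends after day 1 also assume that only 45% of the antibody stays in the circulation.

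Reciprocal titre just after transfusion = donor titre × V / (plasma volume + V). For 1/320 plasma: 320 × 0.4 / 3.9 = 32.8 to 320 × 0.5 / 3.0 = 53.3.

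Decay factor = 0.5^(days elapsed / 21): 0.82 at day 7 (6 days), 0.41 at day 28 (27 days), 0.053 at day 90 (89 days).

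| Donor titre | After transfusion | Day 7 | Day 28 | Day 90 |
|---|---|---|---|---|
| 1/320 | 1/33 to 1/53 | 1/12 to 1/44 | 1/6 to 1/22 | weaker than 1/3 |
| 1/80 | 1/8 to 1/13 | 1/3 to 1/11 | 1/2 to 1/6 | negligible |

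Both donor titres are minimum values, so actual units may carry more. Day 90 is clearly the least affected time point.

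**4. What passive positivity could do to an early comparison**

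Suppose natural conversion p is the same in both arms, plasma turns a share q of the still-negative recipients positive, and 150 per arm are assayed. Plasma-arm positivity is p + (1 − p)q. The chance of a two-sided 5% difference uses the normal approximation with pooled variance under the null.

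| p (assumed) | q = 10% | q = 25% | q = 50% |
|---|---|---|---|
| 70% | 73.0% positive; 8% | 77.5%; 31% | 85.0%; 88% |
| 85% | 86.5% positive; 6% | 88.75%; 16% | 92.5%; 54% |

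The second figure in each cell is the chance of a significant arm difference when plasma has no effect on the patient's own conversion. It runs from close to the nominal 5% to very likely, depending entirely on p and q.

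**The case against.** **The day-90 visit is not settled as a phone call.** Section 9.6.1 reserves the phone for day 365. A reader might infer that day-90 serology is lost; the documents show only that two rules conflict, and under one of them nothing is lost. This objection stands, and it is why the point is a contradiction to reconcile.

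**Passive positivity is an inference.** A reader might infer that days 7 and 28 favour plasma by construction. No assay threshold is given, the residual titre at day 28 is low (1/2 to 1/6 after 1/80 plasma), and section 8 says most patients develop immunity within 15 to 20 days of illness, so surviving controls may be mostly positive by then. This stands as well: the early comparison is ambiguous, and no bias of known size has been shown.

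**Antibody status after transfusion is a legitimate measurement.** For a passive-immunization product it documents exposure. That is true, but section 7.2 asks about sero-conversion, and exposure does not answer that.

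**The t-test label.** A reader might treat the listing of sero-conversion among quantitative variables as a serious error. Section 9.9 already gives chi-square for proportions, and measured titres can be compared quantitatively. In 20,000 simulated trials per scenario, the t-test and chi-square test on yes/no data reached the same decision in every run at 150 and 250 per arm, and differed in at most 2.4% of runs at 50 per arm. It is a wording matter only.

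**Conclusion.** The contradiction is firm: 9.5.12 cannot stand beside 9.5.4.8, the flow chart, the day-90 endpoint in 7.3 and the visit in 9.6.1. Followed literally, it restricts day-90 serology to slow recoverers. The size of the loss is uncertain; 167-300 of about 334 rests on an assumed 50-90% discharged and on day-28 survivors as the base.

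The passive-antibody point supports this rather than standing as a separate failure. Positivity at days 7 and 28 in the plasma arm may include transfused antibody, to an extent set by donor titre and the assay threshold, so it should not be read as the patient's own conversion. It would go too far to say that the endpoint cannot be answered: status by arm can be described at every time point, and endogenous conversion can be assessed at day 90 if serum is obtained.

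The consequence is confined to one secondary endpoint. Day-28 mortality is untouched. The correction should be made while day-90 visits are still to come.

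**What to change.** - Amend 9.5.12 so that the day-90 visit after discharge includes the blood draw, in line with 9.6.1. If that is not feasible, delete day-90 serology from 7.3, 9.5.4.8, the flow chart and the synopsis; do not analyse inpatients only.
- State in 9.5.4.2 that the day-1 antibody sample is drawn before the transfusion.
- Define sero-conversion as a change from negative on that sample to positive at day 90. Compare it as a proportion with the chi-square test that section 9.9 already provides, and move it out of the quantitative list. Say openly that the comparison is conditional on survival to day 90, which the planning rates expect to differ between arms.
- Report days 7 and 28 as antibody level, that is, as exposure, and not as sero-conversion.

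The cost is mostly wording, plus the effort of in-person day-90 visits that 9.6.1 already promises. The downside is fewer evaluable patients, because those already positive at baseline drop out of the comparison, or the loss of one secondary time point if the visit is not feasible.
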